##### Knowledge for Healthy Eating Questionnaire [37]

This questionnaire was developed to assess school-age children’s (6 to 17 years old) declarative knowledge about healthy eating. The questionnaire consists of 15 statements and participants have to rate their agreement regarding each statement (e.g., “Our meal should contain varied and colourful foods”; “Going to school without having breakfast does not interfere with my school performance”). Responses to individual items are scored from 1 (totally disagree) to 5 (totally agree) in a Likert-like format. Responses of each participant are summed to create a composite score ranging from 15 to 75, with higher scores implying more knowledge of healthy eating. The alpha of Cronbach of the original study was 0.73.

##### Satisfaction questionnaire

The research team will develop a satisfaction questionnaire based on previous satisfaction instruments used with this population. The questionnaire will address aspects of utility and feasibility of the program and perceived support by the educational psychologist from the students’ perspective.

#### Weekly assessment

##### Journal

On a weekly basis, children will complete an online journal with specific questions regarding the program and their behaviors. The weekly journal will allow monitoring the individual progress of each child in the program and, simultaneously, to create another moment to reflect about, and consolidate, the learning acquired in the program. Questions will be divided in three sections: (a) invite children to reflect on what they have learnt with the narrative, the synchronous session, and the parental involvement activity of that week according to three types of knowledge [declarative (What I have learnt); procedural (How can I use what I have learnt); and conditional (When can I use in my daily routines what I have learnt)]; (b) questions regarding participants’ cognitive, emotional, and behavioral engagement in the program during the week will also be included; and (c) concrete questions about their food intake will also be covered in the weekly journal.

##### Engagement

Engagement in the program will be assessed with observational measures though the analysis of the interactions of children in the online platform [53]. Examples include number of activities completed, comments to peers’ posts, and others.

### Primary and secondary outcome measures

The primary outcomes will be the analysis of differences in SR, self-efficacy, knowledge towards healthy eating, and, additionally, the amount of healthy and unhealthy food consumption at baseline (*T*_0_), final (*T*_1_), and follow-up (*T*_3_, *T*_4_) assessments. Secondary outcome measures will include the anthropometric (i.e., body mass index [BMI] *Z*-scores), sociodemographic variables (−T_1_), other healthy behaviors (e.g., screen time and physical activity), psychological (e.g., attitudes and perceptions about healthy eating), and engagement (e.g., weekly journal) measures. Differences within the group (i.e., at baseline, final, and follow-ups assessments), as well as between groups (i.e., control, online-intervention, and enhanced-online-intervention), will be tested over time. The repeated measures assessment allows testing relevant factors affecting SR and self-efficacy on healthy eating and food consumption. Additionally, weekly engagement indicators collected with the journals and with the actual interactions with the platform will be tested as predictors of primary outcome measures in final and follow-up assessments. Lastly, moderators and mediators that can affect the outcomes of the intervention but that are not predictor variables include sex, socioeconomic level, and academic achievement.

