**Methods:**

A three-armed randomized controlled trial will be conducted in several schools in Portugal. It will include a standard control group, with no intervention; an online intervention group, with the program for 20 weeks; and an enhanced online intervention group, with the program for 20 weeks embedded with gamification strategies throughout the program. Per research group, 40 groups of about 15 children each will be recruited and measured at five different time points. The three research groups will complete the same assessment protocol at the same timings (baseline, post-intervention, and 3, 6, and 9 months’ follow-ups). The assessment protocol will include anthropometric and psychological measures. The primary outcome measures will be the development of self-regulation skills for healthy eating over time, the development of self-efficacy attitudes, knowledge about healthy eating over time, and others. The secondary outcome measures will include the effect of gamification strategies, engagement, and satisfaction with the program, among others. The program will comprise the following: (i) a weekly group synchronous videoconference session with a trained educational psychologist serving as a mediator and (ii) a weekly parental involvement activity. Narratives, or story-tools, embedded with self-regulation strategies are at the core of the intervention.

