#### The design

This is a 3-arm randomized controlled trial (RCT) with the following: a control group, with no program; an intervention group, with the online narrative-based program; and an enhanced-intervention group, with the online narrative-based program with gamification strategies embedded in the program. Both intervention groups (i.e., the intervention group and the enhanced-intervention group) will have the same narrative-based intervention described in Table 1. The only difference between the two intervention groups is that, in the enhanced online intervention group, gamification strategies will be added to the dynamics of the program. No other intervention components, timings, and materials will differ between these two trial arms. Despite the potential advantages of conducting online interventions, literature on digital interventions to promote behavior change has highlighted that this mode of delivery is associated with high rates of dropout [39]. Thus, one concern among researchers in this field is to devise strategies that mitigate the high rates of dropout and instill engagement in the online intervention [39, 40]. Accordingly, we are implementing the additional gamification strategies in the third group to assess the efficacy of these strategies in promoting engagement with the program and activities.

Gamification consists in the use of game design elements in a non-game context [41]. Non-game contexts can be education [42], health [43], and business [44]. Examples of game design elements are the narrative context, feedback, reputation, ranks, levels, competition, and relational support [41]. Considering the engaging nature of games, it is expected that adding some of their design and motivational features to the non-game contexts [41, 45, 46] will contribute to the (i) creation of engaging and fun contexts or environments, (ii) enhancement of the degree and depth of participants’ engagement, (iii) promotion of learning opportunities, and (iv) motivation of individuals to engage in the task at hand. Table 2 illustrates how gamification was infused in the online program for the enhanced online intervention group.

**Table 2 Tab2:** Gamification elements used in the enhancement-treatment group

Elements*	Objective/rationale**	How it was implemented

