### Goals and expected outcomes

The main purpose of this study is to evaluate the efficacy of an online intervention, narrative-based with or without gamification strategies, designed to promote healthy eating by fostering the use of SR strategies among elementary school-aged children. Thus, the major goals are to promote children’s use of SR strategies for healthy eating, to strengthen their sense of self-efficacy regarding healthy eating, and to increase the consumption of healthy foods. Other goals of the study include the following: increase knowledge about healthy eating and consequences of unhealthy nutrition or lifestyle; contribute to healthier food preferences; and contribute to more positive attitudes and perceptions about healthy eating. Thus, we want to assess the feasibility of conducting an online intervention with this population and examine the advantages of embedding the program with gamification strategies, by comparing it to the program without these strategies.

Overall, it is expected that children taking part of the intervention will, at the end of the intervention, increase their use of SR strategies for healthy eating, enhance their sense of self-efficacy for healthy eating, and increase their consumption of healthy foods. Additionally, it is expected that their knowledge on the topic will increase, that their food preferences become healthier, and that they will display perceptions and attitudes about the topic that are more positive. Lastly, it is expected that participants enrolled in the enhanced-online-intervention group will be more engaged in the intervention than the online-intervention group.

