This study has some strengths worth highlighting. First, it presents an online-based intervention focused on promoting SR skills and strategies to promote healthy eating behaviors among elementary school-aged children. Second, it is conceived as a preventive approach, focused on promoting health-related behaviors, not on treatment. Third, gamification strategies will be implemented to reduce high rates of attrition and low feelings of engagement with the tool. Lastly, the research design foresees an implementation period longer than most of the intervention studies in this domain, with long follow-up. This will allow searching for sustained behavioral changes as a result of the intervention.

There are potential limitations to the present study proposal. First, although we include a weekly journal for participants to complete, during the study it will be difficult to monitor the actual implementation of the strategies trained in the program. Second, full adherence to the program will be a challenge as it implies some level of parental involvement and it lasts for 20 weeks. Third, although the study design is optimized by the selection of relevant psychological variables and the introduction of gamification strategies, the small sample size of this study confers a limited scope to examine full effects. In fact, there is the possibility that smaller effects than anticipated are found. This particular aspect may pose limitations when reflecting about the implications and conclusions of the study. Nevertheless, the study attempts to minimize this aspect by having conducted a priori power analyses. If the present trial shows positive effects at the primary outcomes level, future trials should try to use larger samples, from distinct backgrounds and cultures and include longer follow-up measures (> 6 months).

Altogether, we expect that the results of this study will provide evidence on whether training and fostering SR strategies among elementary school-aged children helps in the promotion of healthy eating habits.

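### Reducing dropout is a stated reason for the gamified arm, but no retention outcome is listed, and journal engagement ratings stop when a child stops taking part

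*Protocol article*

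**What the plan says.** **Purpose of the third arm.** The section The design cites high dropout in digital interventions and the need to "devise strategies that mitigate the high rates of dropout and instill engagement in the online intervention". It then gives the purpose of the gamified arm as "to assess the efficacy of these strategies in promoting engagement with the program and activities". The Discussion lists among the study's strengths that "gamification strategies will be implemented to reduce high rates of attrition and low feelings of engagement with the tool".

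**Hypothesis.** Goals and expected outcomes predicts that "participants enrolled in the enhanced-online-intervention group will be more engaged in the intervention than the online-intervention group".

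**Outcomes.** Primary and secondary outcome measures includes "engagement (e.g., weekly journal) measures" among the secondary outcomes. The abstract says: "The secondary outcome measures will include the effect of gamification strategies, engagement, and satisfaction with the program, among others". Neither list names dropout, retention or attendance.

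**Sources of engagement data.** There are two.
- The Journal section says "On a weekly basis, children will complete an online journal with specific questions regarding the program and their behaviors", and that "questions regarding participants’ cognitive, emotional, and behavioral engagement in the program during the week will also be included".
- The Engagement section adds observation of platform interactions, such as how many activities a child completes.

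In the outcome section, platform interactions appear only where weekly engagement indicators are to be tested as predictors of the primary outcomes.

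**Analysis.** The Statistical analysis plan section applies models like those for the primary outcomes, that is, linear mixed models, to the secondary outcomes.

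**The concern.** There are two linked problems.

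First, one of the two reasons given for a whole randomised arm has no listed outcome that could show success or failure.

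Second, the only example of engagement in the outcome list depends on continued participation. A child who has stopped gives no journal rating, although that child is probably among the least engaged. If gamification keeps reluctant children in the program, their low ratings enter the gamified arm's mean, while similar children are missing from the standard online arm. The better gamification works on retention, the more it pulls down its own journal score.

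At stake is the reading of the only comparison that isolates gamification. A real benefit could be reported as absent or as harm.

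**Working it through.** The article states no dropout rate, no scoring of the journal engagement questions and no expected engagement difference. There is therefore no figure to reproduce, and every value below is an assumption.

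**1. Simple illustration.** Assume an engagement item scored 1 to 5, rated at week 20. The standard online arm keeps 60% of children, with mean 4.0. The gamified arm keeps the same 60%, with mean 4.0, and a further 20% with mean 3.0.
- Standard arm, children still responding: 4.00.
- Gamified arm, children still responding: (0.60 × 4.0 + 0.20 × 3.0) / 0.80 = 3.00 / 0.80 = 3.75.
- Difference: 3.75 − 4.00 = −0.25, although dropout fell from 40% to 20%.

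**2. Range under a selection model.** Let engagement be normal with SD 1. Let the tendency to stay correlate ρ with engagement, and let the top share r stay. The mean among those who stay is μ + ρ·φ(z_r)/r, where φ is the normal density and z_r is the cut-off that leaves share r above it. The bias in gamified minus standard is

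ρ × [φ(z_g)/r_g − φ(z_s)/r_s].

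For r_s = 0.60 the ratio is 0.386/0.60 = 0.644. For r_g = 0.80 it is 0.280/0.80 = 0.350. The bias is therefore −0.294 × ρ.

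| ρ | Bias (SD) | Seen if true benefit is 0.10 | Seen if true benefit is 0.25 |
|---|---|---|---|
| 0.3 | −0.09 | +0.01 | +0.16 |
| 0.5 | −0.15 | −0.05 | +0.10 |
| 0.7 | −0.21 | −0.11 | +0.04 |
| 1.0 | −0.29 | −0.19 | −0.04 |

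A simulation with 200,000 children per arm, ρ = 0.7 and no true effect gave −0.20, in line with the formula.

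Over ρ from 0.3 to 1.0, other retention pairs give:
- 70% versus 80%: −0.04 to −0.15 SD
- 80% versus 90%: −0.05 to −0.16 SD
- 50% versus 70%, or 70% versus 90%: −0.09 to −0.30 SD

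**3. Do platform counts escape this?** Use the step 1 numbers again, now as activities completed per week.
- Counted only in children still active: 4.00 versus 3.75, the same misleading sign.
- Counted over all allocated children, with zero after stopping: 0.60 × 4.0 = 2.40 versus 0.60 × 4.0 + 0.20 × 3.0 = 3.00, a difference of +0.60.

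The sign depends on the denominator. Table 2 adds a separate difficulty: children in the gamified arm earn points for each platform activity, so the intervention directly rewards this count.

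**The case against.** The strongest reply is that engagement is not only the journal. The Engagement section assesses it through platform interactions, and these can be counted for every child with a login. A reader of the outcome list might infer that gamification will be judged only on a measure seen in children still taking part. The article does not support that, because the journal is given there as an example and the second source is described elsewhere. This part of the reply stands.

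It is also fair to say that the stated aim and hypothesis concern engagement, that dropout enters as background and as a strength in the Discussion, and that the abstract's list is open-ended. The objectives therefore do not contradict each other. Whether a stopped child counts as zero or as missing is a scoring detail that an article may leave to the full protocol or analysis plan, and its absence here is no fault in itself.

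Finally, mixed models use each child's earlier ratings, and the illustration allows gamification no effect on children who would have stayed anyway. Both points limit the size. They do not remove the problem: a mixed model corrects only for dropout that earlier observed ratings explain, not for a loss of interest that was never recorded.

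What remains is that the article does state its outcomes, retention is not among them, and the platform counts enter that section only as predictors.

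**Conclusion.** The point holds in a limited form. Reducing dropout is a stated reason for the gamified arm and has no named outcome. A comparison of journal ratings between the two online arms is open to selection that can understate or reverse a benefit.

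Reversal is possible, not established. At 60% versus 80% retention, a true benefit of 0.10 SD changes sign once ρ reaches 0.5. A true benefit of 0.25 SD shrinks to 0.04 SD at ρ = 0.7 and turns negative only at ρ = 1.0. These sizes rest on assumed retention and correlation, on the gamified arm retaining more children, and on a comparison of means among those still responding. A mixed model would reduce the bias by an amount that cannot be judged from the article.

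The change is worth making before the arms are compared, because it gives a direct test of one stated purpose of the third arm.

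**What to change.** - Name program retention as a secondary outcome for enhanced versus standard online intervention. Define it as the week of last participation, and the number of the 20 weeks with session attendance or a completed activity.
- Compute it over all children allocated to the two online arms, with inactive weeks counted as zero.
- Compute the platform counts of the Engagement section on the same basis. Session attendance is a useful part of the retention measure because Table 2 ties points to platform activities and does not mention attendance.
- Report journal engagement ratings as supportive, next to the share of allocated children who completed the journal that week.

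The cost is a change of outcome wording, one more secondary outcome and a little extra analysis. Children answer no new questions. Platform activity is already to be analysed, and attendance at the weekly facilitated sessions needs only to be logged if it is not already.

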### Statistical analysis plan

The effectiveness of the HEP-S intervention will be assessed using linear mixed-effect models. Specifically, we will assess the impact of interventions groups vs. control group on changes over time regarding the primary outcomes (e.g., healthy eating behavior, SR, self-efficacy towards healthy eating). For that, we will first examine within-intervention group differences (i.e., over time) followed by between-intervention group assessments at each time point. Differences between groups will be supported if the beta-weight parameter for the interaction between group and time are statistically significant.

Moreover, statistics descriptive analyses will be computed to describe all participants’ characteristics by using chi-square tests and independent tests to compare groups on the distributions according to sex, age group, BMI *Z*-score classification, and others. In addition, secondary outcomes will be analyzed by using similar models, comparing the three research groups. Also, these secondary repeated measures (e.g., satisfaction with the program) will be examined by conducting an analysis of covariance to explore interference with main outcomes. Finally, no interim analyses of the primary and secondary outcomes are planned to be included in this trial.

All analyses will be completed by using SPSS software (version 26), and *p* values below .05 will be considered statistically significant. The normality, homoscedasticity, and linearity of the residuals of each model will be examined to ensure that the assumptions of the models are met.

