### Proposed sample size

Considering this longitudinal design, in the calculation of the sample, we considered a 0.25 effect size, an alpha level of 0.05, a desired statistical power of 0.8, five measures, and three research groups (i.e., control, online intervention, enhanced online intervention). To run a three-level cluster-randomized trial, previous analysis suggested 40 groups per group condition with 15 participants in each, measured at five different time points (see section “Definition of the hierarchical model”).

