As Heo et al. [54] and others (e.g., [55]) have indicated, the most important goal of a longitudinal intervention is to test whether there are differences between intervention groups with respect to their average growth rates. Applying the approach of these authors, the power to detect a specified treatment difference between average rates of change for the groups is defined as the probability of rejecting the null hypothesis of no treatment-by-linear-trend interaction *H*_0_: γ_101_ = 0, given that it is fact false (γ_101_ ≠ 0). This hypothesis can be tested with
5$$ {F}_o=\frac{{\hat{\gamma}}_{101}^2}{Var\left({\gamma}_{101}\right)}=\frac{\Delta^2\left[{N}_1{N}_2{N}_3 Var(T)\right]}{2\left(1-{\rho}_1\right){\sigma}^2{N}_1 Var(T){\sigma}_{u1}^2}, $$

where Δ is the effect standardized effect size at the last time point, *N*_1_ is the number of level 1 units (repeated measures) per student, *N*_2_ the number of level 2 units (students) per classroom, *N*_3_ the number of level 3 units (classroom) per treatment condition, *Var*(*T*) is the population variance of the time variable *T*, $$ {\upsigma}_{u1}^2 $$ is the three-level random slope variance, σ^2^ is the sum of the other variances, and *ρ*_1_ is the correlation between outcomes measures at different time points on the same student nested within classroom.

The power of the test statistic *F*_0_, denotes 1 − *β*, can be written as follows:
6$$ 1=\beta =\phi \left\{{\left\{\frac{\Delta }{\left({N}_1-1\right)}\left[\frac{\left[{N}_1{N}_2{N}_3 Var(T)\right]}{2\left(1-{\rho}_1\right){\sigma}^2{N}_1 Var(T){\tau}_s}\right]\right.}^{\frac{1}{2}}-{Z}_{1-\left(\alpha /2\right)}\right\}, $$

where τ_*s*_ is the ratio of the three-level random slope variance to the sum of the other variances, ϕ is the cumulative distribution function of a standard normal distribution, and *Z*_1 − (α/2)_ is the 100 (1 − *α*/2) percentile of the standard normal distribution for a bilateral test.

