Consider the following hypothetical values for three-level cluster-randomized trial design parameters: $$ {\upsigma}_e^2=0.5 $$, $$ {\upsigma}_{r0}^2=0.3 $$, $$ {\upsigma}_{r1}^2=0.0 $$, $$ {\upsigma}_{u0}^2=0.2 $$, and $$ {\upsigma}_{u1}^2=0.1 $$. Under the fixed slopes model, the correlation between the outcomes from different student nested within the same classroom is $$ {\uprho}_2={\upsigma}_{u0}^2/\left({\upsigma}_e^2+{\upsigma}_{r0}^2+{\upsigma}_{u0}^2\right)=0.2 $$, whereas the correlation between the outcomes measured at different time points on the same students nested within classrooms is $$ {\uprho}_1={\upsigma}_{r0}^2+{\upsigma}_{u0}^2/\left({\upsigma}_e^2+{\upsigma}_{r0}^2+{\upsigma}_{u0}^2\right)=0.5 $$. Further assumptions are as follows: (a) number of classrooms per treatment condition: *N*_3_ = 40; (b) average number of students per classroom: *N*_3_ = 15; (c) number of repeated measures per student: *N*_1_ = 5; (d) alpha significance level: *α* = 0.05; and (e) statistical power: 1 − *β* = 0.80.

Given design parameters and further assumptions, the minimum detectable effect size is 0.25. In our opinion, an effect size of Δ = .25 is a good first estimate of the smallest effect size of interest in psychological research, since it is not irrelevant and requires a considerable sample size to detect a treatment effect predicted by the researcher.

Finally, we consider that a study with 80% power is a properly powered study, despite several researchers (see, e.g., [56]) consider this a value rather low, as it entails a 20% chance of not finding a theoretically important finding.

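### The planned arm comparisons at each time point are not the test that was powered and, under the printed model, carry any baseline difference; make them supportive and baseline-adjusted

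*Protocol article*

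**What the plan says.** The Statistical analysis plan section of the protocol article assesses the primary outcomes with linear mixed models. It first examines differences within groups over time, "followed by between-intervention group assessments at each time point". Its next sentence gives the decision rule: a difference between groups counts as supported when the group-by-time coefficient is significant.

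Definition of the hierarchical model prints the model. At level 3 the classroom intercept is γ000 + γ001·G + u00 and the classroom slope is γ100 + γ101·G + u10. Baseline is one of the outcome occasions; it is not a covariate.

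The same section defines power as "the probability of rejecting the null hypothesis of no treatment-by-linear-trend interaction", with Δ described thus: it "is the effect standardized effect size at the last time point". It concludes: "Given design parameters and further assumptions, the minimum detectable effect size is 0.25". Proposed sample size repeats the 0.25 with "a desired statistical power of 0.8, five measures, and three research groups", without saying which test the figure belongs to.

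Goals and expected outcomes states the expectation about eating for program end: "it is expected that children taking part of the intervention will, at the end of the intervention, increase their use of SR strategies for healthy". Under Informed consent and randomization, it is schools that are allocated.

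**The concern.** A trend is a contrast within classrooms, so stable differences between classrooms and between students cancel out of it. They do not cancel out of an arm difference at a single visit. Under the printed model that difference at time t is γ001 + γ101·t, and γ001 is the arms' starting difference. Having baseline in the outcome vector adjusts a visit contrast only if the arms are given a common baseline mean, and this model does not impose one.

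With whole schools allocated and a stable classroom share of 20%, some chance imbalance at baseline is to be expected. An unadjusted visit comparison may then show a difference that was already there or obscure one that developed. Because the expectations are worded for the end of the intervention, readers are likely to look at that visit and may carry the 80% over to it. Taken literally, comparing arms at each time point also includes a test at baseline.

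**Working it through.** **Inputs, from Definition of the hierarchical model.** Residual variance 0.5; student intercept 0.3; classroom intercept 0.2; slope variance 0.1; 40 classrooms of 15 students per arm; 5 measures; "alpha significance level: *α* = 0.05", with the "percentile of the standard normal distribution for a bilateral test". Hence ρ1 = 0.5, ρ2 = 0.2 and σ² = 1.

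**Added assumptions.** Time is coded T = 0 to 4 with equal spacing, so Var(T) = 2 and program end is T = 1. Two arms are compared. Classrooms are independent, as in the plan's own calculation.

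**1. The plan's figure.** The slope difference is 0.25/4 = 0.0625.
- Equation 6 as printed multiplies the denominator terms: variance 2(0.5)(5·2·0.1)/(5·15·40·2) = 1/6000. Power is 99.8%, which is not the stated figure.
- Adding the terms instead: 2[0.5 + 5·2·0.1]/6000 = 0.0005, SE 0.02236, z = 2.795. Power is Φ(2.795 − 1.96) = 79.8% and the detectable effect is 0.251. This reproduces 0.25 at 80%.

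In the version that reproduces, the slope variance is averaged over students. I call this the reproducing reading.

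**2. Visit comparison, 0.25 assumed at the visit, fixed slopes.**
- Variance of a classroom mean: V = 0.2 + (0.3 + 0.5)/15 = 0.2533.
- Unadjusted: SE = √(2·0.2533/40) = 0.1125, z = 2.22, power 60.3%, detectable effect 0.315.
- Covariance of the visit mean with the baseline mean: 0.2 + 0.3/15 = 0.22.
- Adjusted variance: 0.2533 − 0.22²/0.2533 = 0.0623. SE = 0.0558, power 99.4%, detectable effect 0.156.
- Reduction in variance: 0.22²/0.2533² = 75%.

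**3. The same at T = 1 on the reproducing reading.**
- V = 0.2 + (0.3 + 0.1 + 0.5)/15 = 0.26. Unadjusted SE = 0.1140, power 59.2%.
- Adjusted variance: 0.26 − 0.22²/0.2533 = 0.0690. SE = 0.0587, power 98.9%.

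**4. Contrast taken from the fitted linear model.** It borrows strength from all five occasions. With fixed slopes at T = 1 the classroom variance is 0.2 + 0.3/15 + (0.5/15)(1/5 + 1/10) = 0.23. SE = 0.1072 and power is about 64%. The classroom variance of 0.2 stays in.

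**5. Later visits, 0.25 still assumed at the visit.**

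| Reading | T | Unadjusted | Adjusted |
|---|---|---|---|
| Reproducing | 2 | 56.1% | 96.3% |
| Reproducing | 4 | 46.2% | 77.6% |
| Slope variance at classroom level | 2 | 28.2% | 37.6% |
| Slope variance at classroom level | 4 | 12.7% | 13.7% |

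If classroom slopes themselves vary, baseline explains less and less of the later differences.

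**6. Effect growing linearly to 0.25 at T = 4.** The program-end effect is then 0.0625. Power at T = 1 is about 8% unadjusted, and 20% (fixed slopes) or 18.5% (reproducing reading) adjusted.

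**The case against.** The strongest reply is that the visit comparisons are not the decision rule. The interaction is, and it is the test that was powered. A stable pre-existing difference falls in γ001 and leaves γ101 alone. That stands. A reader might infer that the trial is underpowered for its stated criterion, or that a baseline imbalance could by itself meet that criterion; the documents support neither.

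Second, the article never says that the visit contrasts are unadjusted, and a condensed article may leave contrast details to a fuller plan. This is partly right. Silence alone would be no finding. The point rests on the model that is printed, whose free group intercept and lack of a baseline term determine what a visit contrast contains.

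Third, a difference of 0.25 at program end is not the plan's assumption. This stands: only the variances are the plan's, and the effect at the visit is added here.

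Fourth, a reader might place the slope variance of 0.1 at classroom level, as the model defines it, and conclude that program-end power is as low as about 47%. That figure cannot be set against the plan's 80%. On the same reading the trend variance is 2[0.5 + 5·15·2·0.1]/6000 = 0.00517, z = 0.87, and the trend test itself has about 14% power. The reading that gives 80% gives 59% at program end.

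**Conclusion.** The point holds as a gap in the wording and a readily available improvement in method. The declared test is not faulted on this ground. Two kinds of arm comparison are planned, only the interaction is powered, and the visit comparisons under the printed model include any starting difference between arms.

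For an assumed difference of 0.25 at a visit, unadjusted power is about 60% with fixed slopes, or 59% at program end on the reproducing reading. Baseline adjustment raises both to about 99%. The gain is smaller later if classroom slopes vary.

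These figures rest on the plan's hypothetical variances, equal spacing of five occasions, independent classrooms and complete data. Allocation by school could add correlation between classrooms of one school, which is not modelled here or in the plan.

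**What to change.** In Statistical analysis plan:
- Keep the group-by-time interaction as the criterion.
- State that the arm contrasts at each visit are supportive.
- Estimate them with baseline adjustment from the same mixed model. Either constrain the arms to a common baseline mean with visit as a categorical factor, or model the post-baseline visits with the child's baseline score and the classroom mean baseline score as covariates.
- Make no arm test at baseline.

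In Proposed sample size and Definition of the hierarchical model, state that 0.25 at 80% power refers to the treatment-by-linear-trend interaction only.

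The cost is wording. Table 3 shows the questionnaire outcomes measured at baseline in all arms, so no extra data or participants are needed. A child without a baseline score would be lost under the covariate form unless that score is imputed; the common-baseline form keeps the child.
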